### Severity of Events

The following definitions should be considered when evaluating the severity of AEs and SAEs:

| Severity of Event | |
| --- | --- |
| Mild | Symptom(s) barely noticeable to subject or does not make subject uncomfortable; does not influence performance or functioning; prescription drug not ordinarily needed for relief of symptom(s) but may be given because of personality of subject. |
| Moderate | Symptom(s) of a sufficient severity to make subject uncomfortable; performance of daily activity is influenced; subject is able to continue in study; treatment for symptom(s) may be needed. |
| Severe | Symptom(s) cause severe discomfort; symptoms cause incapacitation or significant impact on subject’s daily life; severity may cause cessation of treatment with study treatment; treatment for symptom(s) may be given and/or subject hospitalized. |

### Expectedness of Events

Expectedness of all AEs will be determined according to the IB.

## Prescheduled or Elective Procedures or Routinely Scheduled Treatments

A prescheduled or elective procedure or a routinely scheduled treatment will not be considered an SAE, even if the subject is hospitalized; the study site must document all of the following:

- The prescheduled or elective procedure or routinely scheduled treatment was scheduled (or was on a waiting list to be scheduled)prior to obtaining the subject’s consent to participate in the study.
- The condition requiring the prescheduled or elective procedure or routinely scheduled treatment was present before and did not worsen or progress between the subject’s consent to participate in the study and the time of the procedure or treatment.
- The prescheduled or elective procedure or routinely scheduled treatment is the sole reason for the intervention or hospital admission.

## Procedures for Handling Special Situations

### Overdose

An overdose is any dose of study treatment given to a subject or taken by a subject that exceeds the dose described in the protocol. Overdoses are not considered AEs, however, all overdoses should be recorded on an SAE Form and faxed to Biogen Idec within 24 hours. An overdose should be recorded even if it does not result in an AE. Overdoses do not need to be recorded in the CRF.

### Medical Emergency

In a medical emergency requiring immediate attention, study site personnel will apply appropriate medical intervention, according to current standards of care, and contact the <name and phone numbers readacted>

### Contraception Requirements

All male subjects and female subjects of child-bearing potential must practice effective contraception during the study and be willing and able to continue contraception for 2 months after their last dose of study treatment.

For purposes of this study, effective contraception is defined as follows:

For females:

- Using 1 or more of the following acceptable methods of contraception: surgical sterilization (i.e., no uterus and/or ovaries), intrauterine contraception/device, hormonal contraception, or any 2 barrier methods (a combination of male or female condom with spermicide; diaphragm, sponge, cervical cap).
- Abstinence can be considered an acceptable method of contraception at the discretion of the Investigator. Periodic abstinence (e.g., calendar, ovulation, symptothermal, post‑ovulation methods) and withdrawal are not considered acceptable methods of contraception.

For purposes of this study, women of child-bearing potential (WOCBP) are defined as all women physiologically capable of becoming pregnant, **UNLESS** they meet the following conditions:

- Post-menopausal: 12 months of natural (spontaneous) amenorrhea or 6 weeks post surgical bilateral oophorectomy.
- Hysterectomy.

For males:

- Effective male contraception includes a vasectomy with negative semen analysis at follow‑up, or the use of condoms with spermicide.

### Pregnancy

**Subjects should not become pregnant.**

The Investigator must report the pregnancy by faxing the appropriate form to Biogen Idec SABR within 24 hours of the study site staff becoming aware of the pregnancy, at <fax # readacted>The Investigator or study site staff must report the outcome of the pregnancy to Biogen Idec SABR.

Please note that congenital abnormalities/birth defects in the offspring of male of female subjects when conception occurred during study treatment administration should be reported.

### Unblinding for Medical Emergencies

In this study, treatment assignment information is held by the Pharmacist. For medical emergencies, the Investigator will be provided with a set of numbered and sealed code‑break envelopes that will contain the treatment assignment for each enrolled subject.

All treatment assignment information, including code‑break envelopes, must be kept in a secure location.

In a medical emergency when knowledge of the subject’s treatment assignment may possibly influence the subject’s clinical care, the Investigator or designee should attempt to contact the Biogen Idec Medical Director at the contact numbers provided in Section 15.5.2 to discuss the emergency whenever possible. In these instances, the Investigator or designee may open the code‑break envelope that corresponds to the subject experiencing the event. The date and the reasons for opening the code‑break envelope must be submitted to Biogen Idec within 24 hours of the unblinding. Any opened envelopes must be returned to the secure location. Code‑break envelopes will be checked at monitoring visits and will be collected at the end of the study.

The Investigator must document the reasons for unblinding in the subject’s source documents. The Investigator is strongly advised not to divulge the subject’s treatment assignment to any individual not directly involved in managing the medical emergency nor to personnel involved with the analysis and conduct of the study.

### Regulatory Reporting

Suspected Unexpected Serious Adverse Reactions (SUSARs) are SAEs that are unexpected and judged by the Investigator or the Sponsor to be related to the study treatment administered.

SUSARs will be unblinded for reporting to the appropriate authorities and central ethics committees by appropriate personnel in Biogen Idec SABR (or designee). A blinded report will be sent to the Investigator. Personnel involved in the analysis of the study will also remain blinded. The subject may remain in the study and continue to receive study treatment at the Investigator’s discretion. The Investigator should assume that the subject received active treatment when making this decision.

## Investigator Responsibilities

The Investigator’s responsibilities include the following:

- Monitor and record all AEs, including SAEs, regardless of the severity or relationship to study treatment.
- Determine the seriousness, relationship, and severity of each event.
- Determine the onset and resolution dates of each event.
- Monitor and record all pregnancies and follow-up on the outcome of the pregnancy.
- Complete an SAE form for each SAE and fax it to Biogen Idec SABR within 24 hours of the study site staff becoming aware of the event.
- Pursue SAE follow‑up information actively and persistently. Follow‑up information must be reported to Biogen Idec SABR within 24 hours of the study site staff becoming aware of new information.
- Ensure all AE and SAE reports are supported by documentation in the subjects’ medical records.
- Report SAEs to local ethics committees, as required by local law.

## Biogen Idec Responsibilities

Biogen Idec’s responsibilities include the following:

- Before study site activation and subject enrollment, the Clinical Monitor is responsible for reviewing with study site staff the definitions of AE and SAE, as well as the instructions for monitoring, recording, and reporting AEs and SAEs.
- Biogen Idec is to notify all appropriate regulatory authorities, central ethics committees, and the Investigator of SAEs, as required by local law, within required time frames.

# Statistical Statement and Analytical Plan

## Description of Objectives and Endpoints

### Primary Objective and Endpoints

The primary objective of the study is to determine the safety/tolerability profile, systemic PK behavior, and immunogenicity of single IV and SC administrations of BG00010 to sciatica subjects.

The primary safety/tolerability/immunogenicity endpoints are:

- The number and proportion of subjects with AEs.
- Assessment of clinical laboratory parameters.
- Assessment of vital signs.
- Assessment of pain as measured by a Likert numerical pain rating scale.
- Longitudinal assessment of QST (Vibratory, Cool Thermal, and Heat Pain thresholds).
- Assessment of IENFD.

The PK parameters anticipated to be calculated and reported include:

- Cmax: maximum observed serum concentration
- AUC: area under the serum concentration curve
- t½: terminal half-life
- CL: total body clearance
- Vss: steady state volume of distribution

## Demography

All appropriate background data will be summarized by presenting frequency distributions and/or basic summary statistics (mean, standard deviation [SD], median, and range).

## Pharmacokinetics

### Analysis Population

The PK analysis population is defined as all subjects who are randomized and who have been dosed with study treatment and have measurable BG00010 concentrations from at least 1 collected sample.

### Methods of Analysis

PK parameters will be summarized by dose cohort using descriptive statistics to provide an initial assessment of the PK properties of BG00010. PK parameters will be generated for each subject using the concentration versus time data obtained from measurement of BG00010 in blood samples. A validated computer program such as WinNonlin 5.0, or equivalent, will be used to process the data. PK parameters to be calculated will include, but will not be limited to, those noted in Section 16.1.1.

## Safety Data

### Analysis Population

The safety population is defined as all subjects who are randomized and have been dosed with study treatment.

### Methods of Analysis

Adverse Events

The incidence of treatment-emergent AEs and SAEs will be summarized for each dosing cohort overall, by severity, and by relationship to study treatment. The summary tables will include incidence estimates for system organ classes as well as for individual preferred term within each system organ class. A treatment-emergent AE is defined as any AE that has onset on or after dosing with study treatment, or any pre-existing condition that has worsened after dosing with study treatment. SAEs and AEs resulting in withdrawal from the study will be summarized by cohort. AEs will be coded using the Medical Dictionary for Regulatory Activities (MedDRA).

Laboratory Evaluations

Laboratory results that are outside of the normal range for each parameter will be identified and evaluated for their clinical relevance.

Vital Signs

Vital signs will be descriptively examined to determine the incidence of clinically relevant abnormalities, and summarized by cohort.

ECG

A listing of subjects with abnormal ECG status will be presented. Changes from baseline will be summarized by cohort.

Pain Severity Score (Likert)

Change from baseline to endpoint in the severity score from an 11-point Likert scale will be analyzed.

QST

Change from baseline to endpoint in QST will be analyzed. Results will be summarized by cohort and compared with the respective placebo group. Although data from healthy volunteers will not be collected as part of the study, the results from the study will be compared to this background reference population (from published literature) to determine if there are any significant deviations.

IENFD

Change from baseline to endpoint in IENFD will be analyzed. Changes will be summarized by cohort and compared with the respective placebo group as a background reference population.

Physical Examination

A listing of subjects with normal status at baseline, but abnormal status at any time after the date of dosing will be presented.

Clinical Neurological Examination

A listing of subjects with normal status at baseline, but abnormal status at any time after the date of dosing will be presented.

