# Objectives

## Primary Objective

The primary objective of the study is to determine the safety/tolerability profile, systemic PK behavior, and immunogenicity of single IV and SC administrations of BG00010 to sciatica subjects.

The primary safety/tolerability/immunogenicity endpoints are:

- The number and proportion of subjects with adverse events (AEs).
- Assessment of clinical laboratory parameters.
- Assessment of vital signs.
- Assessment of pain as measured by a Likert numerical pain rating scale.
- Longitudinal assessment of the Quantitative Sensory Test (QST; Vibratory, Cool Thermal, and Heat Pain thresholds).
- Assessment of Intra Epidermal Nerve Fiber Density (IENFD).

The PK parameters anticipated to be calculated and reported include:

- Cmax: maximum observed serum concentration
- AUC: area under the serum concentration curve
- t½: terminal half-life
- CL: total body clearance
- Vss: steady state volume of distribution

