The requirement of waiting 24 hours prior to dosing the next subject was based on the animal PK data. As the data suggest that the AUC up to 24 hours accounts for approximately 85% to 99% of the overall AUC following a single‑dose IV or SC administration, a 24‑hour waiting period prior to dosing each subsequent subject is considered sufficient to observe acute treatment-related AEs.

If a subject experiences a treatment-related increase of 4 points from baseline in one of their pain evaluations, a treatment-related SAE, or a treatment-related Grade 3 or higher laboratory AE, the Investigator must contact the Biogen Idec Medical Director prior to dosing the next subject. Dosing will be suspended until the Drug Safety Review Committee (DSRC) completes a safety evaluation (Section 19.2). The decision to continue dosing the cohort will be based on the nature and severity of the SAE or laboratory AE (if applicable), and a review of all available safety data (AEs; all SAEs; vital signs; results for laboratory tests, Likert numerical pain rating assessments, QST, and IENFD).

Four additional subjects (3 for BG00010, 1 for placebo) will be added to an IV cohort if the DSRC requests that additional subjects be added as the result of a DSRC safety review, or if there is a clinical suspicion of a new sensory abnormality (the determination of sensory function will be made by the DSRC using clinical, neurological, QST, and IENFD data).

All study site personnel will be blinded to the subject treatment assignments, with the exception of the Pharmacist or designee who is responsible for preparing the study treatment. If an ad hoc DSRC review is required during the course of dosing a cohort, the Investigator may be unblinded to treatment assignment. The Investigator will be unblinded to treatment assignment after Day 28 for each cohort (see Section 9.3).

Prior to enrollment into the next cohort (the next planned dose level), the DSRC will review unblinded safety data (AEs; all SAEs; vital signs; results for laboratory tests, Likert numerical pain rating assessments, QST, and IENFD) through Day 28, and PK data through Day 5 (or an earlier time point if the concentration drops below the limit of quantification prior to Day 5) from all subjects in the preceding cohorts (see Section 19.2). Enrollment of the next cohort will not begin until the DSRC has approved dosing for that cohort.

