## Randomization and Registration Procedures

Subjects will be randomized after the Investigator has verified that they are eligible per criteria in Sections 8.1 and 8.2. Within each cohort, subjects will be randomized to receive BG00010 or placebo in a 3:1 ratio. The computer-generated Master Randomization List will be prepared by Biogen Idec prior to the start of the study and given to the unblinded Pharmacist. Subjects withdrawn from the study may not be replaced.

The Pharmacist will be responsible for storing the Master Randomization List. Only the unblinded Pharmacist and Pharmacy Site Monitor are to have access to the Master Randomization List. The Master Randomization List must be stored in a locked and secured area.

**No subject may begin treatment prior to enrollment and assignment of a unique subject identification number and randomization that is completed by the unblinded Pharmacist.** The subject identification number will designate study treatment and dose according to the predefined randomization schedule. Any subject identification numbers that are assigned will not be reused even if the subject does not receive treatment. Subjects will be enrolled cohort‑by‑cohort. Biogen Idec or its designee will notify the study site in writing when Cohort B and subsequent cohorts are open for enrollment.

Study treatment will be administered according to the following randomization scheme:

Table 9‑1 Study Treatment Randomization Scheme

| **Cohort** | **BG00010 Dose**  **(g/kg)** | **Number of Doses of Study Treatment** | **Number of Subjects on BG00010** | **Number of Subjects on Placebo** |
| --- | --- | --- | --- | --- |
| A | 0.3 | 1 | 3 | 1 |
| B | 1 | 1 | 3 | 1 |
| C | 3 | 1 | 3 | 1 |
| D | 10 | 1 | 3 | 1 |
| E | 25 | 1 | 3 | 1 |
| F | 50 | 1 | 3 | 1 |
| G | 100 | 1 | 3 | 1 |
| H | 200 | 1 | 3 | 1 |
| I | 400 | 1 | 3 | 1 |
| J | 800 | 1 | 3 | 1 |
| K | 50 (SC) | 1 | 3 | 1 |

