# TREATMENT

## Treatment Schedule

Eleven single-dose cohorts are planned (10 IV and 1 SC). For each cohort, 4 subjects will be randomized to receive 1 adminstration of study treatment (3 subjects will receive BG00010 and 1 subject will receive placebo).

For the dose escalation part of the study, study treatment will be administered as an IV injection by the Investigator or designee.

For the SC administration substudy, study treatment will be administered as up to 4 SC injections (depending on body weight).

BG00010 doses will be escalated according to the cohort design presented in Table 11-1.

Table 11‑2 Planned Cohorts

| **Cohort** | **BG00010 Dose**  **(g/kg)** | **Number of Doses of Study Treatment** | **Number of Subjects on BG00010** | **Number of Subjects on Placebo** |
| --- | --- | --- | --- | --- |
| A | 0.3 | 1 | 3 | 1 |
| B | 1 | 1 | 3 | 1 |
| C | 3 | 1 | 3 | 1 |
| D | 10 | 1 | 3 | 1 |
| Safety Report submitted to the Ethics Committee (Section 11.1.2) | | | | |
| E | 25 | 1 | 3 | 1 |
| F | 50 | 1 | 3 | 1 |
| Safety Report submitted to the Ethics Committee (Section 11.1.2) | | | | |
| G | 100 | 1 | 3 | 1 |
| H | 200 | 1 | 3 | 1 |
| I | 400 | 1 | 3 | 1 |
| J | 800 | 1 | 3 | 1 |
| K* | 50 (SC) | 1 | 3 | 1 |
| * Recruitment to this cohort will commence anytime after all subjects in Cohort G (100 g/kg) have completed their Day 56 visit. | | | | |

Four additional subjects will be added to an IV cohort if the DSRC requests that additional subjects be added as the result of a DSRC safety review, or if there is a clinical suspicion of a new sensory abnormality (the determination of sensory function will be made by the DSRC using clinical, neurological, QST, and IENFD data).

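### QST and IENFD changes are compared with each cohort's own placebo group, which is one subject as planned; placebo pooled over the IV cohorts would be a usable comparator

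*Protocol*

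**What the plan says.** Section 6.1 lists QST ("Longitudinal assessment of the Quantitative Sensory Test") and IENFD among the primary safety endpoints. Section 16.4.2 then sets how they are analyzed. For QST: "Results will be summarized by cohort and compared with the respective placebo group", with a further comparison against published healthy-volunteer data. For IENFD: "Changes will be summarized by cohort and compared with the respective placebo group as a background reference population". The Synopsis gives the same placebo comparator for both.

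The size of that comparator follows from the design. Section 9.2: "Within each cohort, subjects will be randomized to receive BG00010 or placebo in a 3:1 ratio". Section 11.1, for each cohort: "3 subjects will receive BG00010 and 1 subject will receive placebo". Section 7.1 allows expansion: "Four additional subjects (3 for BG00010, 1 for placebo) will be added to an IV cohort if the DSRC requests". Section 11.2 does not assure replacement of subjects who withdraw after dosing, so a cohort could lose its only placebo subject.

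No visible text pools placebo subjects across cohorts. The interim analysis section is redacted and no SAP is at hand.

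For other safety data, Section 16.4.2 names no placebo comparator. Adverse events: "The incidence of treatment-emergent AEs and SAEs will be summarized for each dosing cohort overall, by severity, and by relationship to study treatment". Pain: "Change from baseline to endpoint in the severity score from an 11-point Likert scale will be analyzed".

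**The concern.** A comparison with the cohort's own placebo group means three subjects against one. A group of one has no within-group variance, and its value cannot be told apart from that person's own biological and measurement variation. For IENFD it is the only comparator that the analysis section names.

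The word 'respective' cannot be rescued by reading it as IV placebo versus SC placebo. Section 7.1.1 excludes both QST and IENFD from the SC cohort (Cohort K), so every placebo subject with these data received an IV injection. The natural reading is the placebo subject of the same cohort.

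What is at stake is how the study report reads on two primary safety endpoints. Ten to twenty IV placebo subjects undergo duplicate QST and duplicate skin biopsies, and the stated analysis then uses them one or two at a time.

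**Working it through.** **Plan's own figure.** Ten IV cohorts of 4 plus one SC cohort of 4 gives 10 × 4 + 4 = 44. With every IV cohort expanded to 8, 10 × 8 + 4 = 84. Both ends of the stated range of 44 to 84 reproduce.

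**Placebo subjects with QST and IENFD.** 10 × 1 = 10 as planned, and 10 × 2 = 20 if every IV cohort is expanded. The SC placebo subject has neither test. The figure of 10 applies once all ten IV cohorts are complete.

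**Assumptions.** The protocol gives no SD for the change in QST or IENFD, so results are in units of the between-subject SD, with equal variances in all groups. The 95% level is for illustration; the protocol specifies no interval or test for this contrast.

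**Formula.** Half-width = t(0.975, df) × √(1/n_active + 1/n_placebo), with df = n_active + n_placebo − 2.

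| Comparison | √(1/n_active + 1/n_placebo) | df | t | Half-width (SD) |
|---|---|---|---|---|
| 3 vs 1, own cohort as planned | 1.155 | 2 | 4.303 | 4.97 |
| 6 vs 2, own cohort expanded | 0.816 | 6 | 2.447 | 2.00 |
| 3 vs 10, pooled IV placebo | 0.658 | 11 | 2.201 | 1.45 |
| 6 vs 20, pooled, all expanded | 0.465 | 24 | 2.064 | 0.96 |

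**Is the gain only an effect of 2 df?** Part of it is. The ratio 4.97/1.45 is about 3.4. It is the product of 1.155/0.658 ≈ 1.75 from the standard error and 4.303/2.201 ≈ 1.96 from the t quantile. To remove most of the second part, estimate one SD over all IV groups:

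- Own-cohort placebo: ten active groups of 3 give 10 × 2 = 20 df, and the single placebo subjects add none. Half-width = t(0.975, 20) × 1.155 = 2.41 SD.
- Pooled placebo: 20 + 9 = 29 df. Half-width = t(0.975, 29) × 0.658 = 1.35 SD.

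The own-cohort interval is still about 1.8 times as wide.

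**The same point without a variance assumption.** The most extreme ranking in one direction has exact probability 1/C(4,1) = 1/4 = 0.25 for 3 vs 1, 1/C(8,2) = 1/28 = 0.036 for 6 vs 2, and 1/C(13,3) = 1/286 = 0.0035 for 3 vs 10. With one placebo subject, even complete separation of active from placebo is expected by chance in one cohort out of four.

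**Can the placebo subjects be pooled?** Placebo is saline in all cohorts (Section 10.2), and the IV cohorts share one schedule of assessments. Pooling assumes no material drift in the measurements over calendar time.

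**The case against.** The strongest reply is that this is a descriptive Phase 1 study. Section 16.8 says the sample size has no power basis, and no confidence interval or test of active against placebo is planned. That stands: the half-widths illustrate precision and do not show a failed test. It does not rescue the comparator, because a descriptive comparison with one person is also uninformative.

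A second reply is that the wording is ambiguous. Calling the placebo group a reference population fits one subject poorly, so pooling may have been intended. That is possible, and it is a reason to say so in the text.

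A third reply is that sensory safety does not depend on this contrast. This also stands. The stopping rule in Section 7.3 judges each subject against that subject's own baseline using laboratory normative SDs. QST has a literature reference as well. The safety review committee sees unblinded data from all preceding cohorts before each escalation.

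A reader might be tempted to infer more than the protocol supports:

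- *That pain and adverse events have no placebo comparison, or that adverse event tables merge placebo with active subjects.* Section 16.4.2 is silent on both, and an SAP may settle them.
- *That natural recovery would pass for a drug effect on pain.* Section 5.2 describes recovery in acute sciatica and adds that 10% to 40% develop chronic pain, while entry requires symptoms for at least 6 weeks. Nothing in the protocol sizes such an effect here.
- *That QST and pain are reduced to one time point.* The term endpoint is not defined in Section 16.4.2, and Section 6.1 calls the QST assessment longitudinal. A definition can sit in the SAP.
- *That published and laboratory norms for QST conflict.* One serves a study-level comparison, the other an individual stopping threshold. They can differ.

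**Conclusion.** The point holds for QST and IENFD. The protocol names each cohort's own placebo group as the comparator for two primary safety endpoints. That group is one subject as planned and two after expansion. The 95% half-width is 4.97 SD (2.41 SD with a common SD) for 3 vs 1 and 2.00 SD for 6 vs 2, against 1.45 SD (1.35 SD) for 3 vs 10 with pooled IV placebo. These figures rest on equal variances, on SD units because no SD is given, and on no drift between cohorts.

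It would be too strong to call this a must-fix. Randomization, data collection, escalation and stopping are unaffected, and the same data can be pooled at analysis. It is a cheap improvement. It belongs in the protocol because an SAP that pooled placebo would depart from the protocol's stated comparator.

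**What to change.** In Section 16.4.2 and the Synopsis, replace the cohort-specific placebo comparator for QST and IENFD with placebo pooled over the IV cohorts (10 to 20 subjects), and summarize each BG00010 dose level against it.

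For consistency, give placebo its own column in the adverse event and Likert pain summaries too, with the SC placebo subject listed separately because the route differs.

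The cost is a change of wording, with no added subjects, visits or procedures. The one downside is that pooled placebo subjects are not all concurrent with a given dose cohort. Listing the placebo values by cohort next to the pooled summary lets a reader see any drift.
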